### 2.5. Study endpoints and assessments

#### 2.5.1. Primary endpoint.

The primary endpoint of this study will be changes in the VAS score, defined as the difference in VAS scores from the start of the study and after 8 weeks of treatment.

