### 2.6. Statistical analysis

Based on previous studies of IR pregabalin compared with placebo in patients with DPN,^[20]^ the sample size will be calculated as follows: with a margin of non-inferiority of 9.2 mm, 80% statistical power, and a significance level of 2.5% for 1-sided testing, assuming no difference in VAS scores between the 2 groups and a standard deviation of 0.6, approximately 65 subjects per treatment group will be required to demonstrate non-inferiority. Assuming a 20% dropout rate, 130 participants will be recruited (65 per group).

Full Analysis Set will be used as the main analysis group to evaluate efficacy while Per-Protocol Set will be used as a subanalysis set; Safety Set will be analyzed for safety data.

Differences in VAS scores in each group after 8 weeks of treatment compared with baseline will be described statistically (number of subjects, mean, standard deviation, median, minimum, and maximum) and analyzed by analysis of covariance corrected for baseline as a covariate. SR pregabalin will be considered non-inferior to IR pregabalin if the lower bound of the 95% confidence interval for the least squares mean difference between the treatment groups is greater than the prespecified non-inferiority margin of 9.2 mm. The secondary endpoints will be analyzed using either analysis of covariance or Pearson’s chi-square test, depending on the characteristics of the variables. In addition, demographics, baseline characteristics, treatment compliance, and safety endpoints will be summarized using descriptive statistics. Treatment adherence will be calculated by dividing the number of tablets taken by the number of tablets scheduled for administration and then multiplying by 100. The data will be analyzed using IBM SPSS Statistics for Windows, Version 20 (IBM, Armonk, NY).

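### The non-inferiority rule requires a lower confidence limit above +9.2 mm: wrong sign or wrong bound, so an equivalent SR product would almost never pass

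*Protocol article*

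**What the plan says.** The decision rule is in section 2.6 of the protocol article: "SR pregabalin will be considered non-inferior to IR pregabalin if the lower bound of the 95% confidence interval" and, continuing, "for the least squares mean difference between the treatment groups is greater than the prespecified non-inferiority margin of 9.2 mm". The margin carries no minus sign, and the text does not say whether the difference is SR minus IR or IR minus SR.

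The primary endpoint in section 2.5.1 is the VAS change, "defined as the difference in VAS scores from the start of the study and after 8 weeks of treatment". That does not say which value is subtracted from which.

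The sample size statement in section 2.6 works "with a margin of non-inferiority of 9.2 mm", "80% statistical power" and "a significance level of 2.5% for 1-sided testing", and assumes that the two arms do not truly differ. The abstract's discussion likewise expects the two formulations to be about equally effective. No other section restates the decision rule.

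**The concern.** A non-inferiority test must exclude the possibility that the new product is worse by the margin or more. The printed rule does not do this under either sign convention:

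- **Positive difference = SR worse** (for example SR minus IR, change as week 8 minus baseline). A lower limit above +9.2 mm is evidence that SR is worse by more than the margin, and the rule would call that non-inferior.
- **Positive difference = SR better** (for example reductions scored as positive, SR minus IR). A lower limit above +9.2 mm is evidence of superiority by more than the margin.

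This is the only success criterion for the primary endpoint. Taken literally, it fails an equivalent product or passes a clearly inferior one. The power statement assumes no true difference, so it belongs to a different rule from the one printed.

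**Working it through.** **Inputs from the protocol article.** Section 2.6: margin 9.2 mm, one-sided 2.5%, power 80%, true difference 0, SD 0.6 (no unit), 65 per group, 20% dropout. Section 2.3: VAS of 30 or more marks moderate to severe pain, so higher is worse.

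**Reproducing the plan's sample size.** n per group = 2 × [SD × (1.960 + 0.842) / margin]².

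- SD 0.6: 2 × (0.6 × 2.802 / 9.2)² = 0.07, so 1 per group.
- SD 6 mm (if 0.6 was in cm): 6.7, so 7 per group.

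Neither gives 65, so the stated SD cannot be used to size this problem. Solving for the SD instead, SD = 9.2 / [2.802 × √(2/n)]:

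- n = 52 evaluable (52 / 0.8 = 65 recruited): SD = 16.7 mm.
- n = 65 evaluable: SD = 18.7 mm.

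These SDs are assumptions. SD 25 mm is added as a range check.

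**The printed rule.** SE = SD × √(2/n). The lower limit exceeds +9.2 when the estimate exceeds 9.2 + 1.96 × SE. With true difference 0, the chance of passing is 1 − Φ[(9.2 + 1.96 × SE) / SE].

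**The corrected rule** (upper limit below +9.2 if positive means SR worse; lower limit above −9.2 if positive means SR better). With true difference 0, the chance of passing is Φ(9.2 / SE − 1.96) in both forms.

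| SD (mm) | n per group | SE | Estimate needed, printed rule (mm) | Pass at true 0, printed rule | Pass at true 0, corrected rule |
|---|---|---|---|---|---|
| 16.7 | 52 | 3.28 | 15.6 | 9.3 × 10⁻⁷ | 80.2% |
| 16.7 | 65 | 2.93 | 14.9 | 1.7 × 10⁻⁷ | 88.1% |
| 18.7 | 52 | 3.67 | 16.4 | 3.9 × 10⁻⁶ | 70.8% |
| 18.7 | 65 | 3.28 | 15.6 | 9.5 × 10⁻⁷ | 80.1% |
| 25 | 52 | 4.90 | 18.8 | 6.2 × 10⁻⁵ | 46.7% |
| 25 | 65 | 4.39 | 17.8 | 2.5 × 10⁻⁵ | 55.5% |

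With t instead of normal quantiles, the first four rows need an estimate of 15.0 to 16.5 mm and pass with probability 1.5 × 10⁻⁷ to 3.5 × 10⁻⁶. With SD 0.6 or 6 mm, the printed rule passes with probability zero to machine precision.

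**When the printed rule is met** (SD 16.7, n = 52, positive = SR worse): it passes 2.5% of the time when SR is truly worse by 9.2 mm, 43% when worse by 15 mm and 91% when worse by 20 mm.

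**What the corrected rule gives.** At the two matched pairs (16.7 with 52, 18.7 with 65) it returns about 80% power, and its type I error is 2.5% when SR is worse by exactly 9.2 mm. Both agree with the design statement.

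**The case against.** The strongest reply is that this is a slip of notation with a recoverable intent. The trial is called a non-inferiority study, and the sample size paragraph gives the margin as an unsigned size. The two candidate repairs are the same test under opposite sign conventions. An analyst who saw two nearly identical arms fail would notice the conflict with the power statement. The text also leans towards week 8 minus baseline: section 2.6 compares the 8-week value with baseline, and section 2.5.2 speaks of changes from baseline.

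The intent to test non-inferiority is indeed plain. But the repair is not safe to leave to the reader, because bound, sign and contrast must be set together. Suppose only a minus sign is added (lower limit above −9.2) while change is week 8 minus baseline and the contrast is SR minus IR. A product truly worse by 9.2 mm would then pass about 99.9% of the time instead of 2.5%: for SD 16.7 and n = 52, Φ(18.4 / 3.275 − 1.96) = Φ(3.66). The lean towards week 8 minus baseline makes that mistake more likely. In an open-label trial, settling the direction after data are seen would be hard to defend.

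Three limits on the point do stand:

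- The printed rule is not strictly impossible to meet. It is practically never met when the arms are equal.
- Passing a clearly inferior product depends on literal use with a contrast in which positive means SR is worse.
- Only the protocol article is at hand, so whether the full protocol or the SAP has the same sentence is unknown.

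**Conclusion.** The concern holds and must be fixed. As printed, the primary success criterion is not a non-inferiority rule under either sign convention, and nothing else in the article supplies a valid one. At the design assumption of no true difference, the chance of meeting it is below 0.0004% for SDs of 16.7 to 18.7 mm with 52 to 65 evaluable per group, and below 0.01% at SD 25 mm, against the stated 80%. The exact probabilities rest on assumed SDs and a normal approximation. The conclusion does not: a rule requiring a lower limit above +9.2 mm is invalid whatever the SD. Whether the cause is a dropped minus sign or the wrong bound cannot be told from the text.

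**What to change.** Replace the decision sentence in section 2.6 and make section 2.5.1 match:

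- Define change as week-8 VAS minus baseline VAS.
- Define the contrast as SR minus IR, from the ANCOVA with baseline as covariate.
- Declare SR non-inferior if the **upper** limit of the two-sided 95% confidence interval is below **+9.2 mm**.

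If reductions are to be scored as positive instead, the equivalent rule is a **lower** limit above **−9.2 mm** for SR minus IR. Use one version throughout, including the full protocol and the SAP if they carry the same sentence. The cost is one sentence of text, with no operational change. It should be settled before any outcome data are analysed.

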**Discussion::**

In thus study, we aim to demonstrate that pregabalin SR tablets are associated with better compliance and satisfaction compared with pregabalin IR capsules, despite similar efficacy.

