**Figure 1. F1:**
[figure not shown]
Study design.

The investigator or clinical research coordinator will provide participants with instructions on how to take medication correctly. We will assess medication adherence by determining the amount of study drug not administered at the end of study visit (visit 3). At the final visit, all study drug (leftover tablets and packs) will be collected, and the investigator will check the quantity of the study drug. The number of days between the last visit and end of the treatment period will also be recorded. The percentage of medication adherence will be calculated by dividing the number of pills taken by the number of pills scheduled for administration during the treatment period. If a subject loses their study drug, they must receive a medical examination to confirm the loss, which will then be recorded in the source document and case report form.

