#### 2.5.2. Secondary endpoints.

The secondary endpoints will include the following:

1.Changes from baseline after 8 weeks of treatment in:
a.Quality of life (EQ-5D-3L)^[16]^b.Treatment satisfaction of clinical subjects (Patient Global Impression of Change)c.Treatment satisfaction of the investigator (Clinician Global Impression of Change)d.Sleep disturbance (Daily Sleep Interference Scale)^[17]^e.Medication adherence index (Morisky medication adherence scale 8-item version)^[18]^
2.Frequency, dose, and duration of rescue medication use after administration of the study drug

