## 3. Discussion

We will evaluate the real-world efficacy and safety of SR pregabalin and compare medication adherence among T2DM patients with painful DPN. The SR pregabalin formulation has been developed using a floating and swelling gastro-retentive drug delivery system to prolong the gastric retention of pregabalin, and it can be administered once a day.^[21]^ In a previous randomized double-blind study in South Korean patients with DPN and postherpetic neuralgia, the efficacy of the new SR pregabalin (YHD1119), as measured by the mean Daily Pain Rating Scale score, was non-inferior to IR pregabalin.^[15]^ However, there was no assessment of drug compliance when the IR formulation is switched to the SR formulation from twice-daily to once-daily dosing.

People with chronic conditions, such as cardiovascular disease and diabetes, are frequently confronted with the need to regularly take a substantial number of medications over extended periods of time owing to their underlying disease and other comorbidities.^[22]^ This high pill burden contributes to poor medication adherence, resulting in practice/outcome gaps that limit the expected therapeutic benefits.^[23]^ Previous studies have shown that reducing the frequency of dosing in patients with chronic conditions may enhance medication adherence and clinical outcomes. Therefore, our study aims to evaluate patient adherence to SR pregabalin versus IR pregabalin.^[24]^ In addition, we will evaluate treatment satisfaction from both the patient and physician perspectives after 8 weeks of SR pregabalin therapy. In summary, this randomized, active-controlled, parallel, open-label, multicenter, phase 4 study aims to confirm the real-world efficacy and safety of SR pregabalin in T2DM patients with painful DPN, in addition to evaluate medication adherence.

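### Better compliance with SR is an aim, but pill-count adherence is only described, so the one tested adherence measure is open-label self-report

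*Protocol article*

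**What the plan says.** **The aim.** The abstract's Discussion states: "we aim to demonstrate that pregabalin SR tablets are associated with better compliance and satisfaction compared with pregabalin IR capsules, despite similar efficacy". The abstract's Methods names drug compliance among the secondary outcomes. Section 3 adds that "our study aims to evaluate patient adherence to SR pregabalin versus IR pregabalin", and justifies the trial partly by the lack of a compliance assessment in the earlier double-blind study.

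**The two measures.** Section 2.4 measures adherence from the study drug returned at the final visit, as a percentage "calculated by dividing the number of pills taken by the number of pills scheduled for administration during the treatment period". Section 2.5.2 lists a different measure as item 1e of the secondary endpoints: "Medication adherence index (Morisky medication adherence scale 8-item version". Pill count is not in that list.

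**The analysis.** Section 2.6 states "The secondary endpoints will be analyzed using either analysis of covariance" or Pearson's chi-square test, which covers MMAS-8. It then says that "demographics, baseline characteristics, treatment compliance, and safety endpoints will be summarized using descriptive statistics". The next sentence defines treatment adherence as the tablet-count percentage. The only error rate, power and decision rule in the article belong to the VAS comparison (section 2.5.1: "The primary endpoint of this study will be changes in the VAS score").

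**The concern.** The aim is comparative, yet the rule for pill-count compliance is descriptive. It is grouped with demographics and baseline characteristics, for which no between-arm inference is intended. The compliance aim is left to MMAS-8.

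MMAS-8 is a questionnaire answered by patients who know their treatment. Section 2.3 recruits people already taking IR, so the control arm continues with IR while the SR arm knows it has been moved to a once-daily product. An answer about one's own medication-taking can shift with that knowledge. Returned pill count can be influenced by the patient too, but the investigator checks it and it depends less on opinion. The plan tests the measure more exposed to this bias and leaves the other without a comparison.

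If the two measures disagree, nothing in the article says which one decides whether compliance was better. That choice would then be made with the results in view.

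**Working it through.** **1. The statements side by side**

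| Place in the article | Term used | What it provides |
|---|---|---|
| Abstract, Methods | drug compliance | a secondary outcome, measure not named |
| Abstract, Discussion | compliance | an aim to demonstrate SR better than IR |
| 2.4 | medication adherence | returned pill count, as a percentage |
| 2.5.2, item 1e | medication adherence index | MMAS-8, change from baseline |
| 2.6 | secondary endpoints | ANCOVA or chi-square (includes MMAS-8) |
| 2.6 | treatment compliance | descriptive statistics only |
| 2.6 | treatment adherence | tablet-count percentage |
| 3 | patient adherence | SR versus IR, to be evaluated |

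Section 2.6 names treatment compliance and in the next sentence gives the tablet-count formula. I therefore read treatment compliance as the pill count. MMAS-8 cannot be meant, since it is a listed secondary endpoint with its own analysis rule. So MMAS-8 has a planned test, pill count has none, and no sentence links the compliance aim to either.

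**2. What a pill-count comparison could show**

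The article gives no effect size, SD, alpha or power for adherence, so there is no figure to reproduce. Inputs:

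- 65 recruited per arm and 20% dropout (section 2.6): 65 × 0.8 = 52 evaluable per arm. How the VAS inputs lead to 65 is a separate matter.
- SD of pill-count adherence: not given. Assumed 10, 15 or 20 percentage points.
- Two-sided 95% interval, t multiplier about 1.98.

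Half-width = 1.98 × SD × √(2/52) = 1.98 × SD × 0.196 = 0.388 × SD.

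| Assumed SD | 95% CI half-width |
|---|---|
| 10 points | 3.9 points |
| 15 points | 5.8 points |
| 20 points | 7.8 points |

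Over 8 × 7 = 56 days, a half-width of 5.8 points is about 0.058 × 56 = 3.2 days of dosing.

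**3. What difference could be detected**

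The standardized difference detectable with 80% power at two-sided 5% is (1.96 + 0.84) × √(2/n): 0.49 SD with 65 per arm and 0.55 SD with 52. At 52 per arm this is 0.55 × 10 = 5.5 points for an SD of 10, and 0.55 × 20 = 11.0 points for an SD of 20.

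These are normal-theory approximations. Adherence percentages usually pile up near 100, so they show scale only and are not the proposed analysis. They show that the comparison would be informative without being guaranteed to settle the question.

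**The case against.** **An adherence endpoint already exists.** A reader might infer that the plan designates no adherence measure, or that it cannot support its compliance aim at all. The article does not bear that out: MMAS-8 is a named secondary endpoint with a planned between-arm analysis, and it can give supportive evidence. The abstract's drug compliance may well mean MMAS-8, because it is described there as a change and pill count has no baseline value. This stands. It narrows the point to the untested pill count and the missing link between aim and measure.

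**Describing pill count by arm is ordinary practice.** This is true where pill count serves only drug accountability. Here section 2.4 presents it as the way medication adherence will be assessed, and adherence is one of the trial's stated questions.

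**The wording is strong in one place only.** The verb demonstrate is used of compliance once, in the abstract. Section 3 speaks of evaluating or comparing adherence, and the design and sample size concern VAS. This also stands, and it is why softer wording is an acceptable alternative remedy.

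**Multiplicity.** A reader might infer that the secondary tests are unadjusted and unordered, so that a claim could rest on whichever came out favourably. The article is silent on this. Order and error control for secondary endpoints are commonly left to the analysis plan, which is not shown, so the silence is not a finding. For compliance, moreover, only one listed endpoint is tested; the two global impression scales are labelled satisfaction. A full testing hierarchy gated on VAS non-inferiority would be a design preference, not the correction of an error.

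**Conclusion.** The point holds in a limited form. The article states a comparative compliance aim, fixes a descriptive-only rule for pill-count compliance, omits pill count from the endpoint list, and does not say which of its two adherence measures carries the aim. The only planned adherence test is on self-report under open-label conditions. A between-arm result would therefore support the compliance aim only through the measure more open to knowledge of treatment.

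The size is moderate: the primary VAS analysis is untouched, but one of the trial's stated questions is left with its weaker evidence. The proposed comparison would carry a 95% CI half-width of about 3.9 to 7.8 percentage points. That rests on 52 evaluable patients per arm and an assumed SD of 10 to 20 points, which the article does not supply. The conclusion itself rests on the text and not on these figures. It also depends on reading treatment compliance in section 2.6 as the pill count, which the adjoining formula supports.

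**What to change.** 1. In section 2.6, take treatment compliance out of the descriptive-only list. Add a between-arm comparison of pill-count adherence: the difference with a 95% CI, by a method suited to skewed data such as a bootstrap or a Wilcoxon-based analysis.
2. In section 2.5.2, list pill-count adherence as a secondary endpoint alongside MMAS-8.
3. State before the data are seen whether pill count or MMAS-8 carries the compliance aim. If neither is to be confirmatory, word the compliance conclusion as supportive and replace the claim to demonstrate it in the abstract.

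The cost is a few lines of text. The pill counts are already collected at the final visit, so no visit, assessment or sample-size change is needed. The downside is small: one more secondary comparison, and a compliance claim that stays tied to the named measure even if the other looks better.

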## 3. Discussion

We will evaluate the real-world efficacy and safety of SR pregabalin and compare medication adherence among T2DM patients with painful DPN. The SR pregabalin formulation has been developed using a floating and swelling gastro-retentive drug delivery system to prolong the gastric retention of pregabalin, and it can be administered once a day.^[21]^ In a previous randomized double-blind study in South Korean patients with DPN and postherpetic neuralgia, the efficacy of the new SR pregabalin (YHD1119), as measured by the mean Daily Pain Rating Scale score, was non-inferior to IR pregabalin.^[15]^ However, there was no assessment of drug compliance when the IR formulation is switched to the SR formulation from twice-daily to once-daily dosing.

People with chronic conditions, such as cardiovascular disease and diabetes, are frequently confronted with the need to regularly take a substantial number of medications over extended periods of time owing to their underlying disease and other comorbidities.^[22]^ This high pill burden contributes to poor medication adherence, resulting in practice/outcome gaps that limit the expected therapeutic benefits.^[23]^ Previous studies have shown that reducing the frequency of dosing in patients with chronic conditions may enhance medication adherence and clinical outcomes. Therefore, our study aims to evaluate patient adherence to SR pregabalin versus IR pregabalin.^[24]^ In addition, we will evaluate treatment satisfaction from both the patient and physician perspectives after 8 weeks of SR pregabalin therapy. In summary, this randomized, active-controlled, parallel, open-label, multicenter, phase 4 study aims to confirm the real-world efficacy and safety of SR pregabalin in T2DM patients with painful DPN, in addition to evaluate medication adherence.
